## Abstract

**Background:**

Cigarette smoking remains the leading preventable cause of death, posing heightened risks for vulnerable populations. World Trade Center (WTC) disaster responders face an elevated burden of respiratory diseases, and despite access to an evidence-based tobacco cessation program, a subset continues to smoke cigarettes. Treatment engagement remains a critical barrier, as many people who smoke fail to enroll in or adhere to programs, particularly when participation requires decisions to actively opt-in to treatment. This randomized controlled trial integrates tobacco treatment into an existing low-dose computed tomography (LDCT) lung cancer screening program and compares the effectiveness of an Enhanced Care intervention with opt-out enrollment and biofeedback to Standard Care with opt-in enrollment and standard treatment.

**Methods:**

The trial includes retired Fire Department of the City of New York (FDNY) responders aged 50 years or older who have a smoking history that satisfies either the National Comprehensive Cancer Network criteria of at least 20 pack-years or a simplified criterion of at least 20 years of smoking. Participants are randomized to either Enhanced Care, featuring opt-out enrollment in tobacco treatment with tailored counseling using biofeedback from chest LDCT and spirometry results, or Standard Care, requiring opt-in enrollment and standard tobacco treatment without biofeedback. Both arms receive a varenicline regimen with 4 weeks of pre-loading. Primary outcomes are treatment enrollment and biochemically verified 7-day abstinence. Factors associated with enrollment and abstinence, including retention, adherence, and quit motivation, will be evaluated.

**Discussion:**

This trial addresses a key gap in tobacco cessation research by testing an innovative intervention for a high-risk occupational cohort participating in LDCT screening. The Enhanced Care model integrates opt-out enrollment, personalized biofeedback, and varenicline preloading to reduce smoking rates and health burdens in FDNY responders. Findings aim to inform scalable cessation strategies for both occupational and general populations, highlighting the need for novel approaches for hard-to-treat individuals who smoke.

**Trial registration:**

This trial was registered at ClinicalTrials.gov under the identifier NCT05997225.

**Supplementary Information:**

The online version contains supplementary material available at 10.1186/s13722-025-00598-3.

## Background

On September 11, 2001 (9/11), firefighters and emergency medical service providers (EMS) from the Fire Department of the City of New York (FDNY) were exposed to dense dust and smoke containing fine particulates and carcinogenic chemicals during the World Trade Center (WTC) disaster rescue/recovery efforts [1, 2]. Over the last two decades, many of these rescue/recovery workers have developed health conditions related to this exposure, including respiratory disease [3] and certain cancers [4]. WTC exposure and smoking are both risk factors for these diseases; while WTC exposure is immutable, smoking is a modifiable risk factor. Smoking rates have declined, in part due to initiatives like the ‘Tobacco Free at FDNY’ Program, which, since 2002, has provided free treatment, including medication and intensive counseling services [5]. Despite access to this free program and the well-publicized risks of cancer and lung function decline, a subset of this cohort continues to smoke [6]. 

Research highlights the significant challenges of engaging individuals who smoke in tobacco treatment and achieving abstinence, both of which are critical for cancer reduction and slowing smoking-related lung function decline [7–9]. Many individuals who smoke face barriers to treatment engagement, often failing to enroll in or adhere to available programs, especially when participation requires an active opt-in. Opt-in models frequently fail to reach individuals who are uncertain or lack sufficient motivation to quit. This is especially problematic for high-risk groups like WTC-exposed responders who smoke, where continued tobacco use exacerbates existing health conditions and contributes to poor overall health outcomes. Addressing these challenges necessitates exploring alternative approaches to more effectively engage people who smoke. Growing evidence suggests that opt-out models, which automatically enroll individuals in treatment, significantly boost participation and quit rates [10–12]. 

Integrating tobacco treatment initiatives into existing healthcare programs, such as low-dose chest computed tomography (LDCT) lung cancer screenings, presents a unique opportunity. While LDCT screening has proven effective in reducing lung cancer mortality, it cannot substitute for the preventive benefits of smoking cessation, which remains the most effective strategy against tobacco-related diseases [13, 14]. Despite declining tobacco use across the U.S. and within FDNY, studies have shown that participants in LDCT screening programs tend to quit smoking at lower rates compared with the general population, potentially due to the misconception that screening reduces the necessity of quitting [5, 15, 16]. Professional guidelines and Centers for Medicare and Medicaid Services (CMS) recommendations endorse including tobacco counseling in LDCT lung cancer screening programs [17]. 

Optimal treatment strategies for enhancing cessation outcomes within LDCT screening programs among people who smoke remain unclear [14, 18]. Most programs offer limited support, often restricted to opt-in Quitline referrals, free, confidential telephone counseling services that offer support for smoking cessation, as well as over-the-counter nicotine replacement therapy (NRT). While pilot studies suggest that using LDCT results as motivational biofeedback holds promise [14, 19, 20], the impact of biofeedback that combines results of LDCT screening and lung function testing via spirometry for promoting smoking cessation remains underexplored. Mixed findings from research on spirometry-based lung function feedback highlight the need to evaluate whether integrating both spirometry and LDCT results into counseling can improve treatment outcomes [21–27]. 

Treatment strategies such as opt-out enrollment, biofeedback, and varenicline with preloading have individually demonstrated effectiveness, but their combined impact when bundled into a comprehensive intervention remains untested. This pilot randomized controlled trial (RCT) in high-risk individuals participating in the FDNY-WTC Health Program (WTCHP) LDCT screening program specifically evaluates the effectiveness of this bundled enhanced care model in improving treatment engagement and quit rates compared to standard care.

## Methods

### Study setting

The FDNY-WTCHP offers responders monitoring exams every 12–18 months, a lung cancer Chest LDCT screening program for high-risk individuals with a 20 pack-year history of smoking, and tobacco treatment services, including free access to medications and counseling. Smoking status and pack-year history have been routinely collected since the 9/11 disaster through standardized self-reported questionnaires administered during regular health monitoring visits as part of the FDNY-WTCHP [28]. The current FDNY-WTCHP treatment protocol includes counseling and nicotine replacement therapies (NRT), with varenicline prescribed as needed. Preloading, where medication is initiated prior to target quit date, is recommended, but not required, to reduce cravings and withdrawal symptoms [29]. 

### Source population

The source population includes retired firefighters and EMS over the age of 50 who are currently participating in the FDNY-WTCHP LDCT Screening Program, a federally funded initiative under the National Institute of Occupational Safety and Health (NIOSH). These individuals were present as responders at the WTC disaster site. To avoid any potential undue inducement, trial participation is limited to retired individuals to ensure their involvement remains independent of decisions regarding work-related inducements, such as promotions or overtime bonuses.

### Analytic study population

FDNY-WTCHP participants are eligible for randomization in this trial if they: (1) self-reported smoking either on their most recent survey or at any time within the last five years; (2) have provided prior consent to be contacted for future health research; (3) meet National Comprehensive Cancer Network (NCCN) [30] Group 2 criteria, which require either a 20-pack-year or a 20-year smoking history [31], with the 20-year cutoff selected for its ability to expand screening eligibility, reduce racial disparities, and provide a simpler, more precise measure of smoking exposure [31]. Patients who are undergoing active cancer treatment, have a history of kidney disease or significantly reduced kidney function (eGFR < 30), or have documented varenicline use in the FDNY-WTCHP medication database within the past year are excluded from the study. Individuals who do not meet the entry criteria could still receive treatment through the FDNY Tobacco Cessation Program but are not included in the study.

A flow diagram illustrates participant eligibility and randomization is presented in Fig. 1. Inclusion and exclusion criteria are outlined in Table 1. Following eligibility confirmation, participants are assigned to either Enhanced Care or Standard Care using a 1:1 computer-generated randomization process in a blinded fashion. At the time of writing this manuscript, all preparatory procedures, including randomization, have been finalized, and participant recruitment is actively in progress.

**Fig. 1 Fig1:**
[figure not shown]
Participant Selection and Study Population Flow. **Footnote**: Abbreviation: EGFR, Estimated Glomerular Filtration Rate. The source population includes participants enrolled in the FDNY WTCHP who are retired and aged ≥ 50 years as on 7/1/2024. Some participants have a 20-year smoking history but do not meet the 20 pack-year criterion

**Table 1 Tab1:** Inclusion and exclusion criteria

Inclusion criteria
• Enrolled in the FDNY World Trade Center Health Program (WTCHP)
• Retired
• Age ≥ 50 years
• Self-reported current cigarette smoking
• Smoking history of: o ≥ 20 pack-years (NCCN criteria) OR o ≥ 20 years of smoking duration
**Exclusion criteria**
• Impaired renal function (eGFR < 30 or diagnosed kidney disease)
• Undergoing active cancer treatment
• Following enrollment into the study: o Use of varenicline within the past year o Moderate or high suicide risk (as assessed by Columbia-Suicide Severity Rating Scale, C-SSRS) o Alcohol use disorder (as assessed by Alcohol Use Disorders Identification Test, AUDIT score > 15) • History of adverse effects or intolerability to varenicline • Clinical instability (psychiatric hospitalization within the past year, decompensated cirrhosis, serious cardiovascular disease, history of seizure disorder)

### Participant recruitment

Figure 1 illustrates the flow of participants from the FDNY WTCHP source population to randomization. All eligible participants meeting inclusion criteria are randomized in a 1:1 ratio into Enhanced Care (opt-out) and Standard Care (opt-in) arms. Recruitment letters are mailed and emailed following randomization. For the Enhanced Care group, the recruitment letter informs participants of their selection for opt-out enrollment, specifying all the clinical services offered as part of the study. One month following the mailing of the letters, the research team initiates proactive outreach by phone to explain the study procedures, risks, and benefits, and to conduct the informed consent process. Participants in the Enhanced Care group are informed that clinical services would begin unless they decline participation. Participants who decline to participate or cannot be reached after three attempts will be excluded from the study without further contact.

For the Standard Care (opt-in) group, the recruitment letter explains that participants have been randomly selected to participate in this study, instructing them to contact the research team if interested and to enroll into the study to access the offered clinical services. Only those who actively reach out to the research team will be included in the study with no further study contact.

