### Informed consent

After randomization, participants complete an informed consent, where study procedures, risks, and benefits are explained, emphasizing voluntary participation with no impact on pensions, compensation, or benefits. Consent is provided electronically or verbally (documented and confirmed by letter) for those with platform access challenges, ensuring transparency and engagement.

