### Measures

For Objective 1, which examines factors related to program enrollment, the primary outcome is FDNY Tobacco Cessation Program enrollment (Yes/No), comparing enrollment rates between Enhanced and Standard Care. Sociodemographic factors (sex, age, race, and occupation (firefighter versus EMS)) and clinical factors (LDCT results, spirometry, PTSD, depression, quality of life, prior quit attempts, and nicotine dependence) are measured as potential influences on program enrollment. Additionally, prior program participation and documented quit attempts in health records are recorded.

For Objective 2, which evaluates tobacco abstinence and participant retention across study arms, the primary outcome is biochemically confirmed 7-day point prevalence abstinence, assessed at both the end of treatment and the conclusion of follow-up. Participants receive requisition forms for urine testing at Quest Diagnostics, to be completed within three days prior to appointments. These tests, pre-paid through the FDNY-WTCHP, provide results to the tobacco counselor in the Enhanced Care arm before sessions. The research team assists participants in locating the nearest Quest Diagnostics facility and scheduling appointments as needed. Biomarkers assessed at baseline and prior to each counseling visit include anabasine, nicotine, and its metabolites (cotinine, 3’-hydroxycotinine, and nornicotine) to monitor smoking status and adherence. Cotinine is used to identify tobacco exposure (cutpoint: 20 ng/mL), while anabasine distinguishes active tobacco use from NRT (cutpoint: 2 ng/mL) [50].

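### The text confines the study to post-randomization enrollees, who are selected differently by arm, and no sentence keeps everyone else randomized in the denominator for abstinence

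*Protocol article*

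**What the plan says.** Under Participant recruitment, "All eligible participants meeting inclusion criteria are randomized in a 1:1 ratio into Enhanced Care (opt-out) and Standard Care (opt-in) arms", and "Recruitment letters are mailed and emailed following randomization". The Informed consent section confirms the order: "After randomization, participants complete an informed consent".

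Entry to the study then differs by arm (Participant recruitment):

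- Enhanced Care is telephoned. "Participants who decline to participate or cannot be reached after three attempts will be excluded from the study without further contact".
- Standard Care receives a letter. "Only those who actively reach out to the research team will be included in the study with no further study contact".

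The Ethics statement adds that everyone included has consented. Table 1 lists further exclusions that apply later: "Following enrollment into the study: o Use of varenicline within the past year o Moderate or high suicide risk", with an AUDIT score above 15 as the third sub-item. Analytic study population, which describes eligibility for randomization, says that people who "have documented varenicline use in the FDNY-WTCHP medication database within the past year are excluded from the study".

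Under Measures, Objective 1 compares enrollment (yes/no) by arm. Objective 2 "evaluates tobacco abstinence and participant retention across study arms", with urine-verified 7-day abstinence as its primary outcome. The Abstract also names abstinence as a primary outcome. The urine tests, questionnaires and counseling visits exist only for people who enrolled.

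**The concern.** The way people enter the study is part of what is randomized. The Background says that opt-in offers often miss smokers who are undecided or weakly motivated. On the article's own reasoning, Standard Care enrollees should therefore be a more motivated group than Enhanced Care enrollees, who also include people brought in by telephone.

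If abstinence is compared only among those the text includes in the study, the arms are no longer balanced by randomization on motivation, which is a likely driver of quitting. The bias runs against Enhanced Care. A program that produces more quitters among everyone offered it could look worse on a primary outcome because it reached harder-to-treat people. The limitations in the Discussion cover the consent requirement, extra contact time and bundling, but not this selection.

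**Working it through.** The article states no enrollment rate, quit rate or sample size, so there is no figure to reproduce. Every rate below is an assumption.

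**Set-up.** Let eS be the share enrolling under either offer (always-enrollers) and eE the share enrolling under opt-out. The share enrolling only under opt-out is then eE − eS. This supposes that nobody enrolls under opt-in who would not enroll under opt-out. Let qA be the quit rate in always-enrollers (by arm), qM the rate in opt-out-only enrollees, and q0 a common background rate in non-enrollees.

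- Enrolled-only, Enhanced: (eS × qA,E + (eE − eS) × qM) / eE
- Enrolled-only, Standard: qA,S
- All randomized, Enhanced: eS × qA,E + (eE − eS) × qM + (1 − eE) × q0
- All randomized, Standard: eS × qA,S + (1 − eS) × q0

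**Illustration 1.** eS = 10%, eE = 50%, qA = 40% in both arms, qM = 10%, non-enrollees counted as smoking.

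- Enrolled-only: (0.10 × 0.40 + 0.40 × 0.10) / 0.50 = 16% vs 40%, or −24 points.
- All randomized: 0.04 + 0.04 = 8% vs 0.10 × 0.40 = 4%, or +4 points.

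Varying always-enrollers over 5, 10 and 15%, added enrollment over 20 and 40%, and quit-rate pairs over 40/10, 30/15 and 40/5 gives enrolled-only differences from −8.6 to −31.1 points. The all-randomized differences run from +1.0 to +6.0. Every pair has opt-out-only enrollees quitting less often, so the direction is built in.

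**Illustration 2: Enhanced better among always-enrollers.** eS = 10%, eE = 50%, qA,E = 40%, qA,S = 35%, qM = 10%, q0 = 3%.

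- Enrolled-only: 16.0% vs 35.0%, or −19.0 points.
- All randomized: 8.0 + 0.50 × 3 = 9.5% vs 3.5 + 0.90 × 3 = 6.2%, or +3.3 points.
- The enrolled-only contrast favors Standard whenever qM < (0.35 × 0.50 − 0.10 × 0.40) / 0.40 = 33.75%.

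**Milder case.** eS = 10%, eE = 30%, qA,E = 35%, qA,S = 30%, qM = 20%, q0 = 3%. Enrolled-only is 25.0% vs 30.0% (−5.0); all randomized is 9.6% vs 5.7% (+3.9).

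**Case with no reversal.** All enrollees quit at 30% and q0 = 3%. Enrolled-only is 30% vs 30%. All randomized differs by +5.4 points with eE = 30% and by +10.8 with eE = 50%. The enrolled-only analysis then misses the reach benefit but does not reverse it.

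**Post-enrollment exclusions.** Removing 15% of enrollees in both arms at random in Illustration 2 leaves the enrolled-only difference at −19.0. The all-randomized difference becomes +2.8.

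**Bias from counting non-enrollees as smoking.** With 90% vs 50% not enrolled, this rule favors Enhanced by (0.90 − 0.50) × q0, which is 1.2, 2.0 and 4.0 points at q0 = 3, 5 and 10%. In Illustration 1 with q0 = 10%, the true rates are 8 + 5 = 13% and 4 + 9 = 13%. The true difference is 0 and the rule reports +4.

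**The case against.** The strongest reply is that exclusion from the study is recruitment language. Objective 1 cannot work unless non-enrollees stay in the data. Table 2 explains that people who decline are not contacted again out of respect for their wishes. The section Analytic study population describes people eligible for randomization, and an analysis plan not shown may count everyone. This stands in part: the article never names the Objective 2 denominator, so it would be too strong to say that an enrolled-only analysis is definitely planned. But the only inclusion rule in the text is enrollment, and Objective 2 data come only from enrollees. An analysis of everyone randomized would have to depart from Participant recruitment as worded.

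The trial is also called a pilot, and the Analyses section puts the influence of Enhanced Care on abstinence among exploratory analyses. Measures and the Abstract nevertheless name abstinence a primary outcome.

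A reader might infer more than the text supports:

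- *Screen failures leave by different routes in each arm.* Table 1 applies the same criteria to both. They matter only because they act on differently selected groups.
- *Intolerance and clinical instability are also post-enrollment exclusions.* Their nesting in Table 1 is ambiguous as extracted.
- *The two statements on past-year varenicline use flatly contradict each other.* They can be read as a records screen followed by a later check for other use. The timing needs clarifying.
- *The sign will reverse, or the true benefit is a doubling.* Both depend on assumed rates, and the 8% vs 4% also assumes that no non-enrollee quits.

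**Conclusion.** The point holds for Objective 2. Followed as written, the text leads to a comparison of abstinence and retention between groups selected after randomization by arm-specific routes, and this comparison is not randomized. It can be biased against Enhanced Care, and reverses sign if people who enroll only under opt-out quit sufficiently less often. The Background makes a motivation difference plausible, but nothing in the article fixes its size. The illustrative differences of −24 points among enrollees and +4 among all randomized rest on assumed rates and on counting non-enrollees as smoking. With equal quit rates there is no reversal. Objective 1 is not affected.

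**What to change.** 1. State that the between-arm abstinence analysis includes everyone randomized, in the assigned arm. Decliners, people not reached, non-responders and post-enrollment screen failures stay in the denominator.
2. Prespecify how their outcome is set. Not abstinent is a workable primary rule if its bias towards Enhanced Care is acknowledged (about 1 to 4 points at an assumed 3–10% background quitting).
3. Add sensitivity analyses over a range of background quit rates, and with the smoking status routinely collected at the monitoring exams every 12–18 months, under IRB terms. That status is self-reported, unverified and not aligned with weeks 16 and 28.
4. Label enrolled-only comparisons of abstinence, retention and adherence as descriptive and non-randomized. Retention over everyone randomized would largely re-measure enrollment, so it is no substitute.
5. Clarify between Analytic study population and Table 1 when past-year varenicline use is screened, and whether current smoking is required. The former admits smoking at any time in the last five years, while Table 1 lists current smoking. This bears on step 2, because some non-enrollees may already have quit. Apply exclusions knowable from records before randomization in both arms.

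The cost is protocol and analysis-plan wording, lower headline abstinence percentages and a small data pull. Recruitment is in progress and randomization is complete, so step 5 may have to be a statement of what was done.

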### Informed consent

After randomization, participants complete an informed consent, where study procedures, risks, and benefits are explained, emphasizing voluntary participation with no impact on pensions, compensation, or benefits. Consent is provided electronically or verbally (documented and confirmed by letter) for those with platform access challenges, ensuring transparency and engagement.

